### Strategies to improve adherence to intervention/comparator {15c}

Study products and procedure compliance will be monitored during weekly visits. Participants will be encouraged to discuss any concerns or obstacles associated with the use of the study products. Research staff will emphasize the importance of honest reporting to participants. Subjects will be told that it is crucial for them to report on the use of non-study products, even though it is discouraged. If participants experience difficulties using only study products (e.g., due to taste, withdrawal symptoms), staff will explore the underlying reasons and collaborate with them to develop strategies for overcoming these challenges while adhering to the protocol requirements.

### Concomitant care permitted or prohibited during the trial {15d}

All participants will be provided a handout of Community Health Resources, which include contact information for resources for connecting with behavioral health clinicians to diagnose and manage anxiety and depressive symptoms, as well as information on low-cost medical clinics, housing, and food insecurity. These resources will also include the 24-h intake hotline at Grady Behavioral Health and links provided by the Fulton County Department of Public Health for connecting residents with affordable behavioral health care. Participants recruited at all sites will be instructed to contact their clinician for additional counseling based on Kessler-6 scores indicative of elevated SPD symptom severity [32]. The study coordinator will immediately contact hospital security and clinic staff via the Grady internal hotline to walk any person screened on site expressing self-harm intentions to the emergency department for evaluation.

### Ancillary and post-trial care {34}

During the last visit (end of week 4), participants will be referred to smokefree.gov and given a Tobacco Quitline number.

### Outcomes {16}

#### Primary outcome

The primary outcome is the average number of cigarettes smoked per day (study and non-study cigarettes) based on 7 days’ daily logs submitted through text message prompted surveys during the last week of the trial (before the week 4 visit).

### Secondary outcomes

The following outcomes will be based on 7 days’ daily logs submitted through text message prompted surveys during the last week of the trial (before the week 4 visit). Use of other combusted (e.g., little cigar and cigarillos) and noncombusted (e.g., e-cigarettes) products will be assessed by asking participants to enter an integer indicating the number of each product used per day. Use of nicotine replacement therapy (NRT) or prescription cessation medications will be assessed using a multiple-choice question, allowing participants to select all NRT or prescription cessation medications used from a provided list of options.

The following outcomes will be based on a questionnaire completed during the week 4 visit. Perceived risks of smoking VLNCs will be measured by asking participants’ perceived likelihood of overall harm to health under conditions of smoking VLNCs [33]. Response options range from 1 (Not at all likely) to 5 (Extremely likely), with higher scores representing a better outcome. An additional option, “Don’t know,” is also provided. Self-efficacy to quit smoking will be measured with multiple items, assessing perceptions about the strength of confidence in one’s ability to quit smoking [34]. Response options range from 1 (not at all) to 7 (extremely), with higher scores representing a better outcome. An additional option, “Don’t know,” is also provided. Nicotine dependence will be assessed using the Fagerstrom Test for Nicotine Dependence scale, a six-item questionnaire measuring the quantity of cigarette consumption, the compulsion to use, and dependence [35].

Forgoing cigarettes will be assessed using daily logs submitted throughout the 4 weeks of the trial, with two items asking whether participants chose to skip cigarettes they normally would have smoked and whether they stubbed/butted out a cigarete before finishing it [34, 36]. Response options are as follows: 1 (no), 2 (yes, once), and 3 (yes, several times), with higher scores representing a better outcome. Quit intention will be measured with multiple items asking participants’ intention and motivation to quit in the next month and 6 months [37]. Response options range from 1 (not at all) to 7 (extremely), with higher scores indicating a strong intention to quit. An additional option, “Don’t know,” is also provided.

At weekly visits post randomization, participants will be asked to complete a cigarette evaluation of VLNCs, where participants recall the last time they smoked the study cigarettes and rate subjective effects of the study cigarettes: good taste, satisfaction, dizziness, reduced appetite, nausea, reduced cravings, and enjoyable sensations in the throat and chest at the week 4 visit [38]. Expired breath CO will be measured using Micro + Smokerlyzer™.

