### Objectives {10}

The primary objective of the study is to examine the effect of messages about VLNCs accompanied by VLNC use (vs. use of VLNCs without messages) on the number of cigarettes smoked per day among people who smoke from three groups: those with past-month serious psychological distress (SPD), those with low SES, and those in neither category. The secondary objectives are (1) to examine the effect of messages about VLNCs in combination with VLNC use (vs. use of VLNCs without messages) on the use of other tobacco products (e.g., cigarillos, e-cigarettes), cigarette dependence, and cessation-related outcomes over the study period, and (2) to examine the effect of messages about VLNCs in combination with VLNC use (vs. use of VLNCs without messages) on perceptions and behavioral intentions.

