### Daily logs

From the baseline period through week 4, daily logs will be collected via text messages (sent via Twilio) with links to brief online surveys in REDCap. Daily logs will assess their use of study and non-study cigarettes and other combusted and non-combusted tobacco products. Participants will report tobacco use in the past day.

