**Outcomes**					
Cigarettes per day	x				x
Use of other tobacco products	x				x
Use of cessation medications	x				x
Forgoing cigarettes					x
Quit attempts	x	x	x	x	
Perceived risk of VLNCs	x	x	x	x	
Self-efficacy	x	x	x	x	
Quit intention	x	x	x	x	
Nicotine dependence	x	x	x	x	
Cigarette evaluation	x	x	x	x	
Carbon monoxide	x	x	x	x	

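### Other-product and cessation-medication use: the objective and the power statement cover the four-week period, but the outcome definition counts only the last seven daily logs

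*Protocol article*

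**What the plan says.** All places are in the protocol article.

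- **Objectives {10}**, repeated for the second aim under Hypotheses: the effect of messages on use of other tobacco products, "cigarette dependence, and cessation-related outcomes over the study period".
- **Secondary outcomes**, first paragraph: the outcomes listed there rest on seven days of "daily logs submitted through text message prompted surveys during the last week of the trial (before the week 4 visit". Other combusted and noncombusted products are counted per day under this sentence. So is medication use: "Use of nicotine replacement therapy (NRT) or prescription cessation medications will be assessed using a multiple-choice question".
- **Secondary outcomes**, second paragraph: "The following outcomes will be based on a questionnaire completed during the week 4 visit". Dependence (the Fagerström test) falls here.
- **Secondary outcomes**, third paragraph: "Forgoing cigarettes will be assessed using daily logs submitted throughout the 4 weeks of the trial". Forgoing belongs to the same aim.
- **Daily logs**: "From the baseline period through week 4, daily logs will be collected via text messages".
- **Table 2**: the row "Nicotine dependence" is marked at baseline, randomization, visits 1–3 and visit 4.
- **Sample size {19}**: daily-log outcomes, with other-product use and cessation medications named, are powered on 28 observations per person (d = 0.11–0.17). Visit-based secondary outcomes are powered on 5 (d = 0.27–0.38).
- **Statistical methods {27a}**: secondary outcomes are analysed much as the primary outcome is, by regression. No repeated-measures model is named.

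**The concern.** Three parts of one document should describe the same outcome, and they do not. The objective asks about the period, the power statement assumes all 28 post-randomization days, and the definition keeps the last seven.

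Two consequences follow if the definition is applied as written. First, use confined to weeks 1–3 drops out: a participant who takes NRT in week 2 and stops is scored as a non-user, although the logs recorded it. Second, the claim of power for very small effects belongs to a different outcome from the one defined. A null result on medication or product use could then be read as a well-powered null over the campaign, when it is a less sensitive statement about one week.

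**Working it through.** **1. Sample size inputs.** 262 / 0.8 ≈ 328 and 328 / 0.8 = 410, so the plan's attrition chain reproduces. At 1:1, 262 completers give 131 per arm. Tests are two-sided at 0.05 with power 0.80. Missing daily logs of 0–20% are represented here by n = 131 or 131 × 0.8 = 104.8 per arm.

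**2. The plan's own figure.** For the mean of m daily values with unit variance,

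d = (1.960 + 0.842) × √[(2/n) × VF],

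where VF = (1 + (m − 1)ρ)/m under compound symmetry, or the mean of the correlation matrix ρ^|i−j| under AR(1). The article gives no autocorrelation, so d = 0.11–0.17 cannot be confirmed. One can only solve for the ρ that would produce it.

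Example (compound symmetry, n = 131): with VF = 1, d = 2.802 × √(2/131) = 0.346. For d = 0.11, VF = (0.11/0.346)² = 0.101, so ρ = (28 × 0.101 − 1)/27 = 0.068.

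**3. Same ρ, seven logs.** Continuing the example: VF = (1 + 6 × 0.068)/7 = 0.201 and d = 0.346 × √0.201 = 0.155. All cases:

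| Stated d (28 logs) | Structure | n per arm | Implied ρ | d with 7 logs |
|---|---|---|---|---|
| 0.11 | Compound symmetry | 131 | 0.068 | 0.155 |
| 0.11 | Compound symmetry | 104.8 | 0.047 | 0.166 |
| 0.11 | AR(1) | 131 | 0.496 | 0.203 |
| 0.11 | AR(1) | 104.8 | 0.402 | 0.208 |
| 0.17 | Compound symmetry | 131 | 0.213 | 0.197 |
| 0.17 | Compound symmetry | 104.8 | 0.163 | 0.206 |
| 0.17 | AR(1) | 131 | 0.773 | 0.269 |
| 0.17 | AR(1) | 104.8 | 0.716 | 0.283 |

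Where the plan states 0.11, seven logs give 0.16–0.21. Where it states 0.17, they give 0.20–0.28. No gain from baseline adjustment is counted.

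**4. Dependence at one visit.** With a single measure VF = 1, so d = 0.346 (n = 131) or 0.387 (n = 104.8), against the stated 0.27–0.38 for five visits. The single-visit value lies near or just above the top of that range.

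**5. Any medication use: last week against four weeks.** The weekly rate, odds ratio and persistence are assumptions, because the article gives none. With 131 per arm, the usual two-proportion normal approximation is

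power = Φ{(|p₂ − p₁| − 1.96 × √[2p̄(1 − p̄)/n]) / √[(p₁(1 − p₁) + p₂(1 − p₂))/n]}.

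Take 5% weekly use in control. The odds are 0.0526, doubled 0.1053, giving 9.5% in the message arm.

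- Last week only: 0.050 against 0.095, power 0.29.
- Any use in four independent weeks: 1 − 0.95⁴ = 0.185 against 1 − 0.905⁴ = 0.330, power about 0.76.
- Expected control users: 131 × 0.05 = 6.6 against 131 × 0.185 = 24.3.
- With within-person correlation between weeks (beta-binomial) of 0.2, 0.4 and 0.6, four-week power is 0.65, 0.55 and 0.46.
- Full persistence: the same people use every week, so power stays at 0.29.

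At 3% weekly use, last-week power is 0.20 against 0.58 with independent weeks. At 10% it is 0.48 against 0.93.

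**The case against.** The strongest defence is that an effect over a four-week campaign can reasonably be read at its end, after cumulative exposure, and that the primary outcome uses the same last week. That stands as a defence of the design: a week-4 endpoint is legitimate. It does not remove the conflict. The authors wrote a four-week window for forgoing, under the same aim, and counted 28 days when powering these two outcomes.

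A reader might infer that weeks 1–3 are collected and then ignored. The documents do not support that. The Sample size section treats the earlier days as contributing, forgoing uses them, and quit attempts are asked at every visit. What can be shown is an unresolved contradiction about whether those weeks enter these two outcomes.

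A reader might also infer that dependence must be modelled over all visits. That is a preference: a week-4 score is an ordinary end-of-exposure measure, and the detail of a longitudinal model can be left to the SAP.

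Three further points stand in part. Objective 1 does not name medication use, which is only arguably a cessation-related outcome, although the article lists NRT use as a key secondary outcome. No passage says that NRT use is episodic. And doubled odds is a large effect for campaigns that the article expects to have at most small effects. The power gain in step 5 is therefore an illustration with a wide range, and the independent-weeks figure is its upper end.

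**Conclusion.** The point holds as an internal contradiction for two secondary outcomes: other-product use and NRT or cessation-medication use. The objective and power statement say four weeks; the operative definition says the last seven logs. Under that definition d = 0.11–0.17 does not apply. About d = 0.16–0.28 does, if daily values have equal variance and the autocorrelation is what the stated range implies.

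The size of any power loss for medication use is not established. At 5% weekly use with odds doubled it lies between nothing and the difference between 0.29 and 0.76, depending on persistence.

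For dependence, only the wording and the five-observation basis need reconciling. That power sentence describes visit-based outcomes by type without naming dependence, so the article should say whether it is included. The primary outcome's definition is untouched by this point.

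**What to change.** Preferred: define any NRT or medication use, and mean daily other-product use, over the 28 post-randomization logs, and report the last-week values as supportive. This makes the definition match the objective and the power basis.

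Alternative: keep the week-4 window, say so in Objectives and Hypotheses, and restate the detectable effect for seven observations with the assumed autocorrelation given.

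Either way, leave dependence at week 4 if that is intended, and align the objective and the five-observation power basis with it.

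Cost: revised wording, a matching registry update and modest extra analysis. No new data are needed. The period measure dilutes an effect that appears only late, which the retained last-week value would show. A score of any use across 28 logs also needs a stated rule for missed logs. Recruitment began in September 2025 and data collection is expected to run to January 2029, so the change can be made well before the data are complete.

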### Sample size {19}

In the randomized clinical trial, participants will be randomized into one of two conditions: treatment (VLNCs with messages) or control (VLNCs only). We will conduct three separate trials, each targeting a specific group of people who smoke: (1) individuals with serious psychological distress (SPD), (2) individuals with low SES (defined as having a high school education or less or with household income less than 200% of the federal poverty level), and (3) individuals who are neither of those two groups. For each group, we will have 262 participants to complete the 4-week study. This number accounts for a 20% attrition during the 1-week baseline and an additional 20% attrition during the study period; thus, we will enroll 410 participants and randomize 328 participants to achieve 262 completes for each smoker group. The projected attrition rates are conservative and are based on our own studies and past RCTs with VLNCs [39–41], including with the same priority populations (e.g., 24% attrition during an intensive 8-week study that used ecological momentary assessments in the similar populations in Atlanta, GA [42]; 18% attrition for a 12-week study with smokers with low SES and mental health conditions [13]).

Based on the above assumptions and adjusting for missing data (0–20%) in daily logs, with 262 participants in each participant group completing our study, we will be able to detect the following effect sizes. For data collected in daily logs (28 observations per person): primary outcome (cigarettes per day) and secondary outcomes (use of other tobacco products, cessation medications, and foregoing cigarettes), the study has sufficient (0.80) power to detect small effect sizes (*d* = 0.11–0.17, depending on the level of autocorrelations and missing data). For data collected in weekly in-person visits (5 observations per person): secondary outcomes related to cessation behaviors, perceptions, and physiological responses, the study has sufficient power to detect small-to-medium effect sizes (*d* = 0.27–0.38, depending on the level of autocorrelations and missing data). Cohen’s definition of effect sizes will be used (small *d* = 0.20, medium *d* = 0.50, large *d* = 0.80 [43, 44]).

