### Sequence generation: type of randomisation {21b}

Participates will be stratified by readiness to quit (planning to quit in the next 6 months vs. not) and menthol preference (menthol vs. non-menthol). Within each stratum, participants will be randomized in a 1:1 ratio to either the treatment (VLNCs + messages) or the control (VLNCs only) condition.

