## Statistical methods

### Statistical methods for primary and secondary outcomes {27a}

We will conduct intent-to-treat analysis. All participants who were originally assigned to different treatment conditions are analyzed as part of their original conditions, regardless of whether they completed the treatment or adhered to the protocol. Analyses will be performed using SAS or R software. All statistical tests will be two-tailed (*α* = 0.05). The treatment condition will be compared to the control condition; if significant differences are observed (*p* < 0.05), the results will be interpreted as evidence of treatment effect.

Descriptive statistics for all measurements will be reported separately for each trial (people who smoke with SPD, with low SES, and with neither). Frequency distributions will summarize categorical data, and measures of central tendency and dispersion will summarize continuous data. All data will be examined for bivariate relationships with the outcomes and with each other.

For each trial, the primary analysis will be regression models to test the difference in the mean CPD (cigarettes smoked per day) between those in the treatment condition and those in the control condition, adjusting for the baseline CPD value and other covariates that are strongly correlated with the outcome (*r* ≥ 0.3) [49]. Analyses of secondary outcomes will be similar to the analysis of the primary outcome. We will use multivariable regression models to examine differences between the treatment and the control arm while accounting for potential covariables.

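### Forgoing cigarettes is specified only for the four trial weeks, so its baseline-adjusted analysis has no named baseline, although the daily log already runs in the baseline week

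*Protocol article*

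**What the plan says.** **Forgoing.** The Secondary outcomes section under Outcomes {16} states: "Forgoing cigarettes will be assessed using daily logs submitted throughout the 4 weeks of the trial". Two items are asked, each scored 1 to 3. In Table 2 the forgoing row carries a mark in the daily-log column and nowhere else. The other ten rows in the Outcomes block all have a mark at the baseline visit.

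**The log.** The Daily logs section states: "From the baseline period through week 4, daily logs will be collected via text messages". The paragraph then describes the content as product use and does not name the forgoing items.

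**The analysis.** Statistical methods {27a} describes the primary model for cigarettes per day (CPD) as "adjusting for the baseline CPD value and other covariates that are strongly correlated with the outcome", with a threshold of r ≥ 0.3 for those other covariates. It continues: "Analyses of secondary outcomes will be similar to the analysis of the primary outcome".

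**Status of the outcome.** The Hypotheses section lists more forgoing under messages as one of the predictions of the second aim.

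**The concern.** Read together, these sections promise a baseline-adjusted analysis for an outcome whose baseline the document does not name. Participant timeline {18} counts the baseline week separately from the four weeks of the trial, so on the protocol's own terms the forgoing window excludes it. Sample size {19} agrees, placing forgoing among the outcomes with 28 observations per person.

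A pre-randomization value from the same instrument is usually among the strongest covariates available. Each of the three population groups is analyzed as a separate trial with 262 completers, and Sample size {19} expects messaging campaigns to have at most small effects, so precision counts. The point is also time-sensitive. An analysis plan can choose among variables that were collected, but it cannot create an item that was not asked before randomization. According to Trial status, recruitment began in September 2025 and data collection runs to January 2029, so most of the sample may still be reachable.

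**Working it through.** **1. Are logs collected in the baseline week?** Yes. Besides the text, the compensation in {25b} confirms it. There are 6 visits (baseline, randomization, four weekly) at $50 + $10 each, and $5 per log:

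- 35 logs (7 baseline + 28 trial): 6 × 60 + 35 × 5 = 360 + 175 = $535, the stated maximum.
- 28 logs: 360 + 140 = $500, which does not match.

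**2. Sample size inputs.** Sample size {19}: "thus, we will enroll 410 participants and randomize 328 participants to achieve 262 completes for each smoker group". This reproduces: 262 / 0.8 = 327.5, rounded up to 328, and 328 / 0.8 = 410. Allocation is 1:1, so there are 131 completers per arm in each group. Tests are two-sided at 0.05 ("All statistical tests will be two-tailed"), and Sample size {19} sets power at 0.80.

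**3. The plan's own detectable effect.** For daily-log outcomes it gives d = 0.11–0.17 with 28 observations per person, without stating the autocorrelation, so the figure can be neither reproduced nor refuted. Under equal correlation ρ between days, d = 2.80 × √[(2/131) × (1 + 27ρ)/28], and the stated range corresponds to ρ of about 0.07 to 0.21. These are standard deviations (SDs) of a single day's log. No baseline covariate enters the stated calculation, so the figure says nothing about the present point.

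**4. What a forgoing baseline could add.** Take one outcome per person, the four-week mean of the forgoing items, expressed in SDs of that mean. This is a different scale from step 3.

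- Unadjusted: (1.960 + 0.842) × √(2/131) = 2.802 × 0.1236 = 0.346.
- Adjusted for a baseline with correlation r to the outcome: 0.346 × √(1 − r²).

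The documents give no value of r, so a range is assumed. Its lower end equals the protocol's own covariate threshold.

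| Assumed r | Residual variance, 1 − r² | Reduction | Detectable d | Equivalent N, 262/(1 − r²) |
|---|---|---|---|---|
| 0 (no baseline) | 1.00 | – | 0.346 | 262 |
| 0.3 | 0.91 | 9% | 0.330 | 288 |
| 0.4 | 0.84 | 16% | 0.317 | 312 |
| 0.5 | 0.75 | 25% | 0.300 | 349 |
| 0.6 | 0.64 | 36% | 0.277 | 409 |

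These are upper limits on the gain at each r, because the reference row has no covariates at all.

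**5. CPD.** Table 2 marks CPD both at the baseline visit and in the daily log, and {27a} does not say which one is the baseline value. If it is the baseline-week log mean, the loss is zero. Nothing in the document shows that it is the visit report.

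**The case against.** The strongest reply is that the Secondary outcomes section gives an outcome window, not a collection window. Other product use is defined there by the last seven days only, and nobody infers that those items are missing from earlier logs. Table 2's daily-log column does not exclude the baseline week, and the content description in the Daily logs section is plainly abbreviated. This stands in part: the items may already be asked in the baseline week, and the document does not say that they are absent. It does not answer the point that no forgoing baseline is named anywhere, either as a measurement or as a covariate.

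Second, similar does not mean identical, and {27a} allows other covariates. CPD, dependence, quit intention and readiness to quit are all measured at baseline and could take up part of the gain. This stands, and is why the table gives upper limits. The baseline week is also smoked on normal-nicotine cigarettes and the trial weeks on very low nicotine cigarettes, so a high correlation should not be taken for granted.

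Third, the source of the CPD baseline is a derivation rule that an unseen analysis plan may settle. This stands fully. The protocol repeatedly treats the pre-randomization week as the baseline, so its wording fits the log mean at least as well as the visit report.

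**Conclusion.** The point holds for forgoing alone: as written, the document names no own-baseline value for its analysis, although the vehicle for collecting one is already in place. Under randomization the consequence is some forgone precision, with no bias and no effect on error rates. Its size depends on an assumed correlation of 0.3 to 0.6: at most about 9% to 36% of residual variance, or a detectable d of 0.330 to 0.277 instead of 0.346. With other baseline covariates in the model the gain would normally be smaller. It is zero if the items are already in the baseline-week log and used as a covariate.

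A reader might infer that the daily-log outcomes in general lack a baseline measured the same way, or that the primary analysis loses precision through a pre-product visit report. The documents do not support either. Baseline-week logs are collected for cigarettes and other product use, the primary model does adjust for baseline CPD, and the choice of source is simply not stated. This is a low-priority improvement with one clarification attached.

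**What to change.** 1. State whether the two forgoing items are in the baseline-week logs, and add them if they are not. In {27a} or the analysis plan, adjust the forgoing analysis for their baseline-week mean.
2. As a minor clarification, state in {27a} that the baseline CPD value is the mean of the baseline-week daily logs, counting study and non-study cigarettes as the outcome does.

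The cost is two short items in logs that are already sent and paid for, plus a line of analysis wording. If the items have to be added, participants enrolled before the change will have no forgoing baseline. That gap depends on enrollment date rather than on arm, so the multiple imputation already described in {27c} can cover it. The precision gain would then apply mainly to participants enrolled afterwards, which favors an early change.
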